### Setting

Eligible DS pulmonary TB adult hospitalized for receiving treatment will be assessed for inclusion in the Opti-4TB protocol. The recruitment period will be of 36 months and the patient overall follow-up will be of 6 months covering a total period of 42 months. A control group of 20 LTBI participants will be included.

### Participants

The workflow of the Opti-4TB protocol is described in Figure 1A. Pulmonary TB patients aged 18 or more will be included. Inclusion and Exclusion criteria are listed in Box 1.

**Figure 1 F1:**
[figure not shown]
**(A)** Workflow of immune monitoring and **(B)** sampling schedule of the OPTI-4TB protocol.

Box 1Inclusion and exclusion criteria.
**Box 1:**

Inclusion criteria:
Adult ≥ 18 year-oldPatients having given written consentPatients accepting a follow up ≥ 6 monthsProven active pulmonary tuberculosis (positive direct examination and/or PCR)Or Latent tuberculosis infection assessed by positive IGRA
Exclusion criteria:
Malignant solid tumorMalignant hemopathySolid organ transplantation or hematopoietic stem cell transplantationImmunosuppressive treatments (i.e. biologics, calcineurin inhibitors, corticosteroids)Auto-inflammatory diseaseChronic liver diseasesChronic infection with HIV, HCV (hepatitis C virus) or HBV (hepatitis B virus)Antimycobacterial treatment initiated > 7 daysPregnancy or breastfeedingRefusal to participate to the studyPersons deprived of their liberty by judicial or administrative decisionProtected adultsPatients not affiliated to health-care social securityThe homeless

During the first visit (V1), explanations will be given on treatment duration and schedule of blood sampling occurring at the V1, Day 15 (V2), 2 months (V3) and 6 months (V4) visits to monitor treatment efficacy and tolerance. Additional peripheral blood sampling will be collected at each visit for biomarker assessment as described in Figure 1B.

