## Introduction

Tuberculosis (TB) is a leading cause of death worldwide from infectious disease responsible for approximately 1.5 million deaths yearly (1). Only 5 to 10% of individuals infected with *Mycobacterium tuberculosis* (*Mtb*) will subsequently develop active disease during their lifetime, while the others will have latent TB infection (LTBI). LTBI is detected by interferon (IFN)-γ release assays (IGRAs) such as QuantiFERON-TB (Qiagen®) or T-Spot-TB (Oxford Immunotec®). So far, no test can accurately predict the progression from LTBI to active TB. TB is responsible of a broad spectrum of clinical presentations ranging from minor clinical symptoms to disseminated TB. Lungs are the main disease site accounting for 80% of the cases, although many organs can be affected such as lymph nodes, bones and central nervous system, regardless of lung involvement. TB diagnosis is assessed by the isolation of *Mtb* from patient's specimens either in culture or through molecular methods (2). TB treatment always requires multiple drug regimen administered over a time-period ranging from six to ≥ 18 months, depending on drug susceptibility results. The duration of TB treatment along with related adverse events are the main cause of non-compliance leading to the emergence of multi-drug resistant (MDR)-TB (3).

To date, although sensitivity and specificity are low for predicting failure and relapse, culture conversion of respiratory specimens is still used for treatment efficacy assessment (4, 5). In this context, the World Health Organization (WHO) has adopted in 2015 the “End TB strategy” aiming at reducing the TB-related deaths by 95% and the new contaminations by 90% in 2035 (6). To this end, the WHO encourages the development of new diagnostic and prognostic tools to overcome currently existing tools limitations. The development of these new point-of-care tools should therefore focus on the following objectives:

- to improve the diagnostic sensitivity compared to smear microscopy and sputum culture;- to improve the detection of progression from LTBI to active TB (incipient TB patients);- to accelerate detection of drug resistance to properly guide treatment strategy;- to allow treatment monitoring strategies that provide predictive value for treatment efficacy.

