### Endpoints

To address the objectives mentioned above, the primary endpoint will be to evaluate the concordance of the kinetics of the biomarkers with the outcome of treated TB patients at each visit. It is a composite outcome including clinical status, radiological computed tomography (CT)-scan assessment and mycobacterial culture conversion of sputum samples.

This will comprise:

1) A whole blood transcriptomic signature based on levels of expression of a panel of 6 genes;2) A proteomic signature based on levels of various cytokines and chemokines production measured in plasma;3) A dynamic phenotypic monitoring of circulating T cell subpopulations through spectral cytometry using a panel of 30 markers;

Secondary endpoints will be to identify profiles, based on the above biomarkers, consistent with three *Mtb* infection stages: LTBI, active TB and cured TB.

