### Variables

The following data will be recorded in an Opti-4TB specific electronic Case Report Form (e-CRF): demographics and comorbidities, TB clinical characteristics including symptoms, localization(s) of the lesions, biological and CT-scan findings, anti-TB regimen, and associated therapies. TB microbiological characteristics will include the type of lineage and species of the *M. tuberculosis complex* and the type of sample from which the pathogen has been isolated along with phenotypic and genotypic drug-resistance profile determination. The latter will be obtained through whole genome sequencing (WGS) of each isolate which will also enable the monitoring of *Mtb* micro-diversity (including antibiotic resistance mutations) emergence within each host throughout the treatment.

The PCR-based transcriptomic assay will measure transcripts expression levels of a 6 gene panel named RISK-6 by quantitative real-time (qRT) PCR at each time point (20). The panel includes the following genes: *GBP2, FCGR1B, SERPING1, TUBGCP6, TRMT2A*, and *SDR39U1*. The RISK6 signature score is based on a calculation algorithm taking as input data the cycle thresholds ratio for 9 different pairs of transcripts.

The proteomic assay will measure cytokines and chemokines concentration levels in plasma at each time point using the Bio-Plex Pro™ Human Cytokine 27-plex Assay (Bio-Rad, USA). Cytokines and chemokines will be measured, after whole blood stimulations with either QuantiFERON-Gold Plus kit or an in-House “Heparin-Binding HaemAgglutinin” (HBHA) antigen (21). The concentration levels of IFN-γ measured in this assay will also serve as reference for a double IGRA assay combining the different stimulations mentioned.

The quantitative and functional characteristics of T-cell subpopulations will be assessed by spectral cytometry (Aurora, Cytek® Biosciences, USA) on fixed cells obtained from blood samples taken at each time point and previously stimulated as above-mentioned. A 30 markers panel will be used to identify and quantify each subtype of T-cells. An equal number of total cell events will be recorded to enable comparison between patients and timepoints.

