For the proteomic and the T-cell phenotyping assays, whole blood collected in heparin tubes (BD Vacutainer® Heparin Tube, BD, USA) will be transferred into QuantiFERON Gold plus kit (QFT-P) tubes for stimulation. QFT-P includes four blood collection tubes: NIL, TB1, TB2, and Mitogen each requiring 1 mL of whole blood. NIL tubes contain no antigens and are used as a negative control. TB1 and TB2 tubes contains the conventional ESAT-6 and CFP-10 antigens, designed to produce cell-mediated immune responses from CD4+ T lymphocytes (22). In addition, TB2 also contains an undisclosed peptide pool that can stimulate both CD4+ and CD8+ T-cells (23). The mitogen tube contains phyto-hemagglutinin used as positive control. An extra 1 mL of whole blood will be stimulated with 10 μg/mL of rmsHBHA. After a 24 h-stimulation (37 °C, 5% CO2 atmosphere) plasma and cells from each of the five conditions will be separated by decantation. Plasma will be stored at −80°C awaiting batch serial cytokine and chemokine quantification with the Bio-Plex Pro™ Human Cytokine 27-plex Assay. Collected cells will be transferred into new tubes and incubated with FACS lysing buffer (Becton Dickinson, USA) to lyse red blood cells and fix all peripheral blood mononuclear cells (PBMCs) and fixed white blood cells pellets will be stored at −80°C until further use. In preparation for flow cytometry, cells will be resuspended and aliquoted for staining. In addition, 100 μL of cell suspension will be aliquoted for unstained controls. A previously described 29-marker panel of antibodies with the addition of a CD19 marker will be used for staining (18). Briefly, the panel contains 28 T-cell oriented surface markers (lineage markers, chemokine receptors, activation markers and exhaustion markers), one intracellular target (perforin) and CD19 to improve resolution (antibodies purchased from BD Bioscience, USA, BioLegend, USA and ThermoFisher Scientific, USA). Cells will be resuspended in Brilliant Stain Buffer (BD Bioscience, USA), stained for 30 min at room temperature in the dark, washed with FACS buffer (PBS 0.1% BSA) and fixed with 4% Formaldehyde (FA) (ThermoFisher Scientific, USA) before intracellular staining in BD PhosFlow Perm/Wash Buffer I (BD Bioscience, USA). Then samples will be fixed for 20 min in freshly reconstituted 1% FA, washed once with PBS, resuspended in FACS buffer, and kept at 4°C until acquisition on Aurora Cytek® spectral analyzer.

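### In the LTBI/active/cured profiles (secondary endpoint), IFN-γ from the TB1/TB2 tubes and its close correlates are not independent LTBI-versus-TB discriminators, because only the LTBI controls are selected on IGRA

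*Protocol article*

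**What the plan says.** - **Entry.** Box 1 takes controls on "Latent tuberculosis infection assessed by positive IGRA". Active TB patients qualify by positive direct examination and/or PCR, and no IGRA result is asked of them. The Introduction makes IGRA the working definition of latency: "LTBI is detected by interferon (IFN)-γ release assays (IGRAs) such as QuantiFERON-TB", with T-Spot-TB as the other example. Box 1 does not name a platform.
- **Biomarkers.** Under Variables: "Cytokines and chemokines will be measured, after whole blood stimulations with either QuantiFERON-Gold Plus kit or an in-House" HBHA antigen, and "The concentration levels of IFN-γ measured in this assay will also serve as reference for a double IGRA assay". Under Biomarker assays: "TB1 and TB2 tubes contains the conventional ESAT-6 and CFP-10 antigens". The other conditions do not use those antigens: "NIL tubes contain no antigens and are used as a negative control", "The mitogen tube contains phyto-hemagglutinin used as positive control", and HBHA is a separate stimulation. RISK-6 comes from separate RNA tubes.
- **Use of the controls.** The secondary endpoint is to find biomarker profiles for the "infection stages: LTBI, active TB and cured TB". The primary endpoint sets biomarker kinetics against outcome in treated TB patients and has no LTBI comparison.
- **Limitations.** The Discussion names blood rather than lung sampling, and the number of variables relative to the sample size. It does not mention that the entry test for controls overlaps with a biomarker.

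**The concern.** A positive IGRA means an IFN-γ response above a cut-off. Requiring it of controls but not of TB patients removes the low tail from one group only. If the two populations responded identically to ESAT-6/CFP-10, the selected controls would still show higher TB1/TB2 IFN-γ than the unselected patients. Any cytokine that moves with IFN-γ inherits part of that shift. The shift has a direction: it can create or exaggerate an excess in LTBI, and it can hide an excess in TB.

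At stake is the latency signature, one of the stated deliverables and the one that needs the 20 controls. If TB1/TB2 IFN-γ enters it, part of its apparent performance restates the inclusion criterion. The planned multicentre validation study could then carry that part forward.

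**Working it through.** **Figure in the plan.** There is none to reproduce. The group sizes of 40 and 20 rest on precedent and feasibility, without an effect size, SD or power.

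**Inputs from the protocol article.** 40 TB and 20 LTBI (Study sample size); non-parametric comparison for the double IGRA and immunomonitoring data (same section); two-sided p < 0.05 (Statistical methods).

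**Assumed inputs.** q is the share of TB patients below the IGRA cut-off, taken as 5%, 10%, 20% and 30%. ρ is the correlation between the entry IGRA and the study readout. The document gives neither.

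**Null model.** LTBI and TB have the same distribution of antigen-stimulated response. LTBI is truncated below its q-quantile on the entry IGRA, and TB is not truncated.

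**Step 1, AUC at ρ = 1.** A share q of TB patients lies below every control. The remaining 1 − q has the same distribution as the controls. Hence

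AUC = P(LTBI > TB) = q × 1 + (1 − q) × 0.5 = 0.5 + q/2.

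This gives 0.5 + 0.05/2 = 0.525, 0.5 + 0.10/2 = 0.55, 0.5 + 0.20/2 = 0.60 and 0.5 + 0.30/2 = 0.65.

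**Step 2, false-positive rate.** Simulated two-sided Mann-Whitney test, 40 versus 20, nominal 5%, normal scores. Repeat simulations agree to within about two percentage points.

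| q (assumed) | AUC, ρ = 1 | Error, ρ = 1 | Error, ρ = 0.7 | Error, ρ = 0.5 | Error, ρ = 0 |
|---|---|---|---|---|---|
| 5% | 0.525 | 5% | 5% | 5% | 5% |
| 10% | 0.55 | 8–9% | 7% | 6% | 5% |
| 20% | 0.60 | 22% | 13% | 9% | 5% |
| 30% | 0.65 | 48% | 23% | 14% | 5% |

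The ρ = 1 column applies to TB1/TB2 IFN-γ only if the entry IGRA and the study readout are in effect the same measurement. The ρ = 0 column shows that a readout unrelated to the entry IGRA carries no bias.

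**Step 3, restricting TB to patients IGRA-positive at V1.**
- *LTBI versus active (V1).* Both groups are now truncated alike. AUC returns to 0.50 and the error to about 5%.
- *LTBI versus cured (V4).* Truncation at V1 carries over to V4 only in part. At q = 30%, ρ = 1 and an assumed V1–V4 correlation of 0.5, AUC is still about 0.57 and the error about 12%.
- *TB patients left.* 40 × (1 − q) = 38, 36, 32 and 28 for the four values of q.

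**The case against.** **IGRA defines LTBI here.** The document gives no other way to identify latent infection, so Box 1 follows its own case definition. That stands, and the entry rule is not an error. But a test that defines a group cannot also count as independent evidence that separates the group.

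**The reach is limited.** A reader might infer that all stimulated cytokines, or the study's main analysis, are biased by construction. The documents do not support that. HBHA and mitogen readouts do not use the entry antigens and are touched only through correlation with the entry IGRA. RISK-6 is measured in separate, unstimulated blood. The primary endpoint and the within-TB kinetics make no LTBI comparison.

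**The largest figures are the worst case.** This also stands. The 48% needs both the highest assumed q and perfect correlation. The entry IGRA may have been T-Spot-TB or a separate QuantiFERON draw, while the study reads IFN-γ on a 27-plex assay, so ρ may well be below 1. At q = 5% the effect disappears.

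**The V1 restriction is imperfect.** It does not fully repair LTBI versus cured. A low response in active TB may be a true disease signal, which the restriction would discard. The document also gives no IGRA cut-off for the multiplex readout. These points argue for a sensitivity analysis rather than a replacement of the main comparison.

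**It is analysis-plan detail.** Only in part. Which cytokines enter which classifier can be left to the SAP. The entry rule, the biomarker list and the three-stage comparison are all fixed in this article, and the overlap follows from them.

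**Conclusion.** The point holds in a narrow form. For the secondary stage-profile endpoint, TB1/TB2 IFN-γ, the QuantiFERON half of the double IGRA and closely correlated cytokines cannot be read as unbiased LTBI-versus-TB discriminators. The importance ranges from negligible to serious, and the documents cannot place it within that range because they give neither q nor ρ. The figures rest on identical true response distributions, the assumed q and ρ, and a rank test on 40 versus 20. The study can narrow the uncertainty itself, since its V1 measurements in TB patients should largely show what q is.

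A reader might also infer that the latency signature cannot transfer to other patients. That is not shown: a signature built on IGRA-positive controls still applies to latent infection as this document defines it.

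**What to change.** Keep Box 1 as it is. For the stage-profile analysis:

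1. Report the LTBI-versus-active and LTBI-versus-cured signatures with TB1/TB2 IFN-γ excluded, and do not count it as evidence for the latency signature.
2. For the other TB1/TB2 cytokines and the double IGRA, add an LTBI-versus-active sensitivity analysis restricted to TB patients IGRA-positive at V1, by the assay and cut-off used for LTBI entry where available. Report the IGRA-negative share.
3. For LTBI versus cured, state that restriction at V1 does not fully remove the bias, and interpret these readouts with that caveat.
4. Leave RISK-6, the within-TB analyses and the primary endpoint unchanged, with all patients kept.

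The cost is analysis wording, plus an IGRA result at V1 on the entry platform if that differs from the study readout. The one sensitivity analysis loses about 5% to 30% of its TB patients (assumed; 38 down to 28 of 40) and may lose a true low-response signal. The main comparison therefore keeps everyone.

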### Endpoints

To address the objectives mentioned above, the primary endpoint will be to evaluate the concordance of the kinetics of the biomarkers with the outcome of treated TB patients at each visit. It is a composite outcome including clinical status, radiological computed tomography (CT)-scan assessment and mycobacterial culture conversion of sputum samples.

This will comprise:

1) A whole blood transcriptomic signature based on levels of expression of a panel of 6 genes;2) A proteomic signature based on levels of various cytokines and chemokines production measured in plasma;3) A dynamic phenotypic monitoring of circulating T cell subpopulations through spectral cytometry using a panel of 30 markers;

Secondary endpoints will be to identify profiles, based on the above biomarkers, consistent with three *Mtb* infection stages: LTBI, active TB and cured TB.

### Variables

The following data will be recorded in an Opti-4TB specific electronic Case Report Form (e-CRF): demographics and comorbidities, TB clinical characteristics including symptoms, localization(s) of the lesions, biological and CT-scan findings, anti-TB regimen, and associated therapies. TB microbiological characteristics will include the type of lineage and species of the *M. tuberculosis complex* and the type of sample from which the pathogen has been isolated along with phenotypic and genotypic drug-resistance profile determination. The latter will be obtained through whole genome sequencing (WGS) of each isolate which will also enable the monitoring of *Mtb* micro-diversity (including antibiotic resistance mutations) emergence within each host throughout the treatment.

The PCR-based transcriptomic assay will measure transcripts expression levels of a 6 gene panel named RISK-6 by quantitative real-time (qRT) PCR at each time point (20). The panel includes the following genes: *GBP2, FCGR1B, SERPING1, TUBGCP6, TRMT2A*, and *SDR39U1*. The RISK6 signature score is based on a calculation algorithm taking as input data the cycle thresholds ratio for 9 different pairs of transcripts.

The proteomic assay will measure cytokines and chemokines concentration levels in plasma at each time point using the Bio-Plex Pro™ Human Cytokine 27-plex Assay (Bio-Rad, USA). Cytokines and chemokines will be measured, after whole blood stimulations with either QuantiFERON-Gold Plus kit or an in-House “Heparin-Binding HaemAgglutinin” (HBHA) antigen (21). The concentration levels of IFN-γ measured in this assay will also serve as reference for a double IGRA assay combining the different stimulations mentioned.

The quantitative and functional characteristics of T-cell subpopulations will be assessed by spectral cytometry (Aurora, Cytek® Biosciences, USA) on fixed cells obtained from blood samples taken at each time point and previously stimulated as above-mentioned. A 30 markers panel will be used to identify and quantify each subtype of T-cells. An equal number of total cell events will be recorded to enable comparison between patients and timepoints.

### Biomarker assays

As previously stated, three different assays will be performed to evaluate the performance of immune biomarkers in TB diagnosis and outcome.

For the transcriptomic assay, whole blood will be collected on specific Tempus Blood RNA tubes (Thermo Fischer Scientific, USA) containing a liquid RNA stabilization reagent providing *in situ* stabilization of RNA and transcript profile within the blood samples. These samples will be used to perform qRT-PCR and calculate the RISK-6 score.

For the proteomic and the T-cell phenotyping assays, whole blood collected in heparin tubes (BD Vacutainer® Heparin Tube, BD, USA) will be transferred into QuantiFERON Gold plus kit (QFT-P) tubes for stimulation. QFT-P includes four blood collection tubes: NIL, TB1, TB2, and Mitogen each requiring 1 mL of whole blood. NIL tubes contain no antigens and are used as a negative control. TB1 and TB2 tubes contains the conventional ESAT-6 and CFP-10 antigens, designed to produce cell-mediated immune responses from CD4+ T lymphocytes (22). In addition, TB2 also contains an undisclosed peptide pool that can stimulate both CD4+ and CD8+ T-cells (23). The mitogen tube contains phyto-hemagglutinin used as positive control. An extra 1 mL of whole blood will be stimulated with 10 μg/mL of rmsHBHA. After a 24 h-stimulation (37 °C, 5% CO2 atmosphere) plasma and cells from each of the five conditions will be separated by decantation. Plasma will be stored at −80°C awaiting batch serial cytokine and chemokine quantification with the Bio-Plex Pro™ Human Cytokine 27-plex Assay. Collected cells will be transferred into new tubes and incubated with FACS lysing buffer (Becton Dickinson, USA) to lyse red blood cells and fix all peripheral blood mononuclear cells (PBMCs) and fixed white blood cells pellets will be stored at −80°C until further use. In preparation for flow cytometry, cells will be resuspended and aliquoted for staining. In addition, 100 μL of cell suspension will be aliquoted for unstained controls. A previously described 29-marker panel of antibodies with the addition of a CD19 marker will be used for staining (18). Briefly, the panel contains 28 T-cell oriented surface markers (lineage markers, chemokine receptors, activation markers and exhaustion markers), one intracellular target (perforin) and CD19 to improve resolution (antibodies purchased from BD Bioscience, USA, BioLegend, USA and ThermoFisher Scientific, USA). Cells will be resuspended in Brilliant Stain Buffer (BD Bioscience, USA), stained for 30 min at room temperature in the dark, washed with FACS buffer (PBS 0.1% BSA) and fixed with 4% Formaldehyde (FA) (ThermoFisher Scientific, USA) before intracellular staining in BD PhosFlow Perm/Wash Buffer I (BD Bioscience, USA). Then samples will be fixed for 20 min in freshly reconstituted 1% FA, washed once with PBS, resuspended in FACS buffer, and kept at 4°C until acquisition on Aurora Cytek® spectral analyzer.

